# Investigating the effects of synbiotic supplementation on functional movement, strength and muscle health in older Australians: a study protocol for a double-blind, randomized, placebo-controlled trial

**DOI:** 10.1186/s13063-024-08130-9

**Published:** 2024-05-07

**Keywords:** Synbiotic, Microbiome, Sarcopenia, Muscle mass, Muscle strength, Physical performance, Gut-muscle axis

## Abstract

**Background:**

Aging has been associated with a progressive loss of skeletal muscle quality, quantity and strength, which may result in a condition known as sarcopenia, leading to a decline in physical performance, loss of independence and reduced quality of life. While the cause of impaired physical functioning observed in elderly populations appears to be multifactorial, recent evidence suggests that age-associated alterations in gut microbiota could be a contributing factor. The primary objective will be to assess the effects of a dietary synbiotic formulation on sarcopenia-related functional outcomes such as handgrip strength, gait speed and physical performance within older individuals living independently. The secondary objective will be to examine associations between changes in gut microbiota composition, functional performance and lean muscle mass.

**Methods:**

Seventy-four elderly (60–85 years) participants will be randomized in a double-blind, placebo-controlled fashion to either an intervention or control group. The intervention group (*n* = 37) will receive oral synbiotic formulation daily for 16 weeks. The control group (*n* = 37) will receive placebo. Assessments of physical performance (including Short Physical Performance Battery, handgrip strength and timed up-and-go tests) and muscle ultrasonography will be performed at 4 time points (baseline and weeks 8, 16 and 20). Likewise, body composition via bioelectric impedance analysis and blood and stool samples will be collected at each time point. Dual-energy X-ray absorptiometry will be performed at baseline and week 16. The primary outcomes will be between-group changes in physical performance from baseline to 16 weeks. Secondary outcomes include changes in body composition, muscle mass and architecture, fecal microbiota composition and diversity, and fecal and plasma metabolomics.

**Discussion:**

Gut-modulating supplements appear to be effective in modifying gut microbiota composition in healthy older adults. However, it is unclear whether these changes translate into functional and/or health improvements. In the present study, we will investigate the effects of a synbiotic formulation on measures of physical performance, strength and muscle health in healthy older populations.

**Trial registration:**

This study was prospectively registered with the Australian New Zealand Clinical Trials Registry (ACTRN12622000652774) in May 2022.

**Supplementary Information:**

The online version contains supplementary material available at 10.1186/s13063-024-08130-9.

## Background

The global demographic is experiencing a shift to an older population with increased life expectancy. As we age, we observe a progressive loss of muscle mass, strength, and physical function which can have many health implications, a condition known as sarcopenia. The term, *sarcopenia*, was proposed by Irwin Rosenberg to describe the age-related decline in skeletal muscle and physical performance [1]. The reported prevalence of sarcopenia in the literature appears to vary due to different criteria for diagnosis [2, 3] and heterogeneity of study populations [4]. A recent meta-analysis estimated a global prevalence of sarcopenia in older adults (≥ 60 years) between 10 and 27% [5], with another suggesting an overall prevalence of 10% in the general population [6]. The latter findings are similar to those of a 2020 meta-analysis by Papadopoulou and colleagues which reported prevalence rates of 9 and 11% in community-dwelling women and men, respectively [7]. Diminished muscle strength has been more closely tied to impaired physical function and poor outcomes than reduced muscle mass in the revised European Working Group on Sarcopenia in Older People (EWGSOP2) consensus definition of sarcopenia [8]. EWGSOP2 [8] criteria propose a diagnosis of sarcopenia is *probable* with low muscle strength (i.e., reduced grip strength) and this diagnosis is *confirmed* with the identification of low muscle mass (quantity). Sarcopenia is considered *severe* if reduced physical performance (i.e., slow gait speed) is identified in conjunction with reduced skeletal muscle strength and mass according to these revised EWGSOP2 criteria.

While the cause of age-related changes in muscle mass and physical functioning is likely multifactorial, recent evidence suggests that alteration in gut microbiota may play a role [9, 10]. It has been estimated that the human gastrointestinal tract (GIT) contains approximately 10^14^ microorganisms with more than 1000 distinct bacterial species [11]. While *Bacteroidetes*, *Firmicutes*, *Proteobacteria*, and *Actinobacteria* are the predominant bacterial phyla represented in the gut microbiota [12], each person (host) appears to have a unique biological relationship with its microbiota [13]. Analyzing fecal samples obtained from 728 older women, Jackson et al. found a negative association between host frailty and microbiota diversity [14]. The gut-muscle axis has received attention recently with suggestions that the composition and diversity of gut microbiota can be a determinant of skeletal muscle mass and metabolism [9]. Emerging evidence, predominantly in pre-clinical models, suggests disruption to the balance between microbial communities, such as depletion of symbionts and commensal bacteria and over-representation of opportunistic pathogens (such as those seen in gut dysbiosis), may contribute to the aforementioned age-related changes [9, 15, 16]. Indeed, with advancing age, where malnutrition, inactivity and chronic diseases are often experienced, gut dysbiosis is observed [17]. Conversely, individuals with successful aging, such as centenarians, demonstrate elevated representation of “good” bacteria, such as *Bifidobacteria* [18].

Few studies have explored the gut-muscle axis in humans, especially within the elderly. Bacterial taxa such as *Enterobacteriaceae*, *Bacteroides*, and *Prevotella*, have been correlated with measures of gait speed [15]. A 2022 study found that the diversity and composition of gut microbiota in community-dwelling older adults was associated with sarcopenia [19]. Claesson et al. demonstrated that physical performance was inversely related to species richness of the fecal microbiota of 178 older subjects [20]. Analysis of data from 371 ELDERMET cohort subjects revealed an association between the presence of frailty in community-dwelling elderly individuals and comparable gut microbiome profiles of nursing home residents [21]. Furthermore, an adequate representation of *Bifidobacterium* has shown to be fundamental for the production of butyrate [22], a short-chain fatty acid (SCFA) with important anti-inflammatory and pro-anabolic activities involved in the gut-muscle axis. Treatment with butyrate appears to protect against age-related muscle atrophy [23], which supports the idea that pre- and/or probiotic supplementation, known to increase the abundance of *Bifidobacterium* and butyrate producers in older individuals [24, 25], may protect against physical performance deficits with aging [16]. Despite this, there is a scarcity of research evaluating the effect of gut-modulating supplements in older populations. A recent systematic review found no clear evidence of benefit in physical performance in 5 studies evaluating the use of pre-, pro-, or synbiotics in older adults [26]. Notwithstanding, 12 weeks of consuming a synbiotic increased SCFA production compared with a placebo in elderly individuals in a 2013 study [27]. In a more recent trial, 13 weeks of consuming a prebiotic improved handgrip strength compared with placebo [28] which suggests the potential for prebiotic supplementation as a treatment for deficits in age-related muscle function. Similarly, ingestion of a multi-strain probiotic for 12 weeks resulted in significant improvements in physical performance (timed up and go (TUG) test, gait speed) and decreased risk of falls compared with placebo [29].

Skeletal muscle mass and strength loss and functional impairment with advancing age are linked to several chronic diseases and associated with a higher chance of falls/fractures [30], loss of independence [31] and the likelihood of requiring long−term care due to reduced mobility, disability, and/or hospitalization [32, 33]. Since older adults are the fastest−growing global subpopulation, modulation of the microbiome through dietary administration of pre−, pro−, or synbiotics may represent a promising approach to counterbalance the loss of muscle mass and function seen with aging [34]. This manuscript describes the evaluation of synbiotic supplementation on physical performance measures compared with placebo according to the Standard Protocol Items: Recommendations for Intervention Trials (SPIRIT) reporting guidelines [35].

## Methods

### Study design

We will carry out a randomized, placebo-controlled, double-blinded superiority study to evaluate the effects of a synbiotic formulation on measures of physical performance, strength and muscle health in older, independent living individuals. This clinical trial was registered with the Australian New Zealand Clinical Trials Registry (ACTRN12622000652774) in May 2022 and the study design, protocol, and informed consent procedures were approved by the Human Research Ethics Committee of Swinburne University of Technology (Ref. 20226246–9780).

### Study setting

This clinical trial will take place at Swinburne University of Technology, Hawthorn campus. Dual-energy X-ray absorptiometry (DXA) evaluations will be conducted at Deakin University, Burwood campus. Recruitment commenced in November 2022 and the enrolment target is expected to be met in April 2024. The schedule of enrolment, interventions, and assessments is shown in Fig. 1.

**Fig. 1 Fig1:**
[figure not shown]
Schedule of enrolment, interventions, and assessments (adopted from SPIRIT 2013 Figure). ^1^include age, gender, COVID-19 history and vaccine status; ^2^include heart rate, and blood pressure; ^3^include handgrip strength, 4m gait speed, balance testing, repeat chair stands, timed up and go; ^4^via bioelectric impedance analysis; ^5^include SARC-F, Physical Activity Scale for the Elderly, Gastrointestinal Symptom Rating Scale, Constipation Assessment Scale; ^6^include stool sample and blood sample. IP: investigational product

#### Study intervention

All eligible participants will be randomized equally (1:1) into either treatment (synbiotic) or control (placebo) groups. The study treatment will consist of a multi-strain synbiotic (SYN) powder containing inulin and a combination of probiotic strains. Placebo (PLA) will consist of maltodextrin, which will match synbiotic in appearance, taste, and consistency. Both SYN and PLA sachets will be 1800 mg. The participants will be instructed to consume 1 sachet daily (orally, dissolved in water, and at the same time each day) for the entire intervention period. Both SYN and matching PLA will be provided by Lallemand Health Solutions (Montreal, QC, Canada). Enrolled participants will be asked to make no changes to their current exercise habits or usual dietary intakes and abstain from taking any dietary supplements containing prebiotics and/or probiotics during the study. A list of prohibited medications is provided in Supplementary File 1.

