### Secondary outcome measure: dietary assessment

Habitual dietary intake will be recorded by participants using 3-day dietary intakes for the days leading up to each of the 4 study appointments. Dietary intake data will be analyzed to discern energy intake, and macro- and micro-nutrients. Participants will also complete the Australian Eating Survey [77] food frequency questionnaire at baseline only and before randomization to establish pre-intervention dietary patterns.

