Wilcoxon’s signed-rank test, Spearman’s rank correlation (p), Pearson’s correlation (r), multiple linear regression, and/or linear mixed models will be used to examine associations and appropriate comparisons depending on the distributions of the variables. Relationships between markers of functional performance, ordinations of stool microbiota composition, and stool/plasma metabolites will also be assessed using the Structural Equation Model to enable causal assumptions to be interpreted between variables to ensure these relationships are not “coincidental” and linear mixed models. All mixed models will include the subject as a random factor and time as a continuous covariate. Backward stepwise regression will be used to identify the strongest predictors of changes in aspects of functional performance. The false discovery rate for all tests will be controlled by adjusting *P* values using the Benjamini–Hochberg procedure. Adjusted *P* values will be presented as *Q* values. Statistical analyses will be completed using SPSS v.26. 11.2.2

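### No stated gut–muscle association model has a term for change in diet or physical activity, yet the structural equation model is said to rule out coincidental links

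*Protocol article*

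**What the plan says.** All references are to the protocol article.

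- **Objective.** The Abstract (Background) gives the secondary objective as to "examine associations between changes in gut microbiota composition, functional performance and lean muscle mass". These are change-on-change associations.
- **Safeguard.** Study intervention states: "Enrolled participants will be asked to make no changes to their current exercise habits or usual dietary intakes". This is a request to participants, and no analysis is tied to it.
- **Link to dysbiosis.** The Background section notes that "with advancing age, where malnutrition, inactivity and chronic diseases are often experienced, gut dysbiosis is observed".
- **Diet data.** The dietary assessment section states: "Habitual dietary intake will be recorded by participants using 3-day dietary intakes for the days leading up to each of the 4 study appointments". It continues: "Dietary intake data will be analyzed to discern energy intake, and macro- and micro-nutrients". No model is named for the results.
- **Activity data.** The Fig. 1 legend lists the questionnaires, which "include SARC-F, Physical Activity Scale for the Elderly, Gastrointestinal Symptom Rating Scale, Constipation Assessment Scale". The figure itself is not shown.
- **Models.** Statistical analyses and power offers rank and product-moment correlation, multiple linear regression and mixed models, chosen by distribution. It adds: "All mixed models will include the subject as a random factor and time as a continuous covariate". It names functional performance, stool microbiota ordinations and stool or plasma metabolites as the SEM variables, and says the SEM supports causal interpretation and shows that the relationships are not coincidental. It also plans a backward stepwise regression whose candidate predictors are not listed, and Benjamini–Hochberg adjustment throughout.

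**The concern.** Diet and activity can plausibly move both sides of the association under study. A participant who eats differently or becomes more active between visits may show a change in stool composition and, separately, a change in gait, chair rise or lean mass. If neither variable is in the model, the two changes correlate and the correlation looks like a gut–muscle link. This can happen within either arm, including placebo alone.

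What makes this more than a missing covariate list is the positive claim made for the SEM. An SEM does not test whether a common cause has been left out. It assumes that none has. With function, microbiota and metabolites as the only variables, it cannot separate a direct path from a shared driver that the trial has measured but left outside the model. At stake is the interpretation of the secondary objective, which could be reported in causal language when the shared driver is diet or activity.

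**Working it through.** **1. Do the stated terms already deal with it?**

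| Stated control | What it handles | Change in diet or activity during the trial? |
|---|---|---|
| Subject as random factor | Stable differences between people | No: the change is within a person |
| Time as continuous covariate | A trend common to all participants | No: the change differs between people |
| Control of baseline group differences | Imbalance at entry | No: the change comes after baseline |
| Benjamini–Hochberg | Multiplicity of chance findings | No: the marginal correlation is real |
| Randomisation | The arm comparison | No: change-on-change associations are not randomised |
| SEM on three sets of variables | Paths among those variables | No: diet and activity are not among them |

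**2. How large could it be?** The plan gives no figure on this point, so there is none to reproduce. Inputs:

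- n = 52 completers, from 74 × (1 − 0.30) = 51.8; n = 74 as the upper case.
- Two-sided test at 5%.
- Assumption: change in diet or activity (C) correlates r with microbiota change (M) and r with functional change (F), and M and F are independent given C. The documents give no value for r.

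Under this model the induced correlation between M and F is r × r = r². Rejection rates from simulation, 20,000 runs per cell:

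| r | Induced correlation r² | n = 52, unadjusted | n = 74, unadjusted | Adjusted for error-free C |
|---|---|---|---|---|
| 0.2 | 0.04 | 6% | 6–7% | about 5% |
| 0.3 | 0.09 | 9% | 11–12% | about 5% |
| 0.4 | 0.16 | 20% | 28% | about 5% |
| 0.5 | 0.25 | 43% | 58% | about 5% |

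Ranges show two independent simulation runs. Hand check by Fisher's transformation for r = 0.5, n = 52: atanh(0.25) × √(52 − 3) = 0.2554 × 7 = 1.79, and P(Z > 1.96 − 1.79) ≈ 0.43, which agrees.

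**3. What if C is measured with error?** Three-day records and a questionnaire score are imperfect. Assume reliability 0.5 and r = 0.5. The product of the two observed correlations with C is 0.5² × 0.5 = 0.125. The partial correlation left after adjustment is (0.25 − 0.125)/(1 − 0.125) = 0.125/0.875 = 0.14. At n = 52 this gives 0.144 × √(52 − 1 − 3) ≈ 1.00, so the test rejects in about 17% of trials. That is well below 43% but not 5%.

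**4. Cost of adjusting.** With four covariates that explain nothing, the residual variance factor is (n − 2)/(n − 6): 50/46 = 1.087 at n = 52 and 72/68 = 1.059 at n = 74.

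**The case against.** The best counter-argument is that this rests on silence. A covariate list for secondary association models is commonly left to the analysis plan, which is not shown, and the article condenses a longer protocol. Much of this stands:

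- A reader might infer that diet and activity enter no analysis at all. The text does not establish that. Covariates of the multiple regression and candidates for the stepwise regression are unlisted and could include them, and the mixed-model sentence may state a minimum. The gap is firm only where variables are named, chiefly in the SEM.
- A reader might infer that the protocol names diet as a cause of dysbiosis. It names malnutrition and inactivity, and only as accompanying dysbiosis in ageing. People at risk of malnutrition are excluded at entry.
- Repeated PASE measurement is an inference. PASE shares a footnote with SARC-F, which is completed at every visit, but no text says the same of PASE.
- The instruction on diet and exercise is a sound safeguard, not the defect. Eligibility also requires participants to avoid probiotic foods from screening onwards. That controls one part of diet, but for a habitual consumer it is itself a dietary change, some of which may come before baseline.
- Examining an association is legitimate, and the marginal association in the simulation is real. A rejection is an error only if it is read as a direct gut–muscle link.

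The last point brings the SEM statement back in. That sentence invites exactly this reading, and deferral to an analysis plan does not answer a claim that the protocol itself makes.

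**Conclusion.** The point holds in a limited form. The named association models leave out change in diet and activity, and the claim that the SEM shows links not to be coincidental is one those models cannot support. Under the assumed structure the distortion is small for r of 0.2 to 0.3 (6% to 9% at n = 52) and serious from 0.4 upwards (20% to 43%). Every r is an assumption, so none of these rates is an estimate for this trial. Adjustment removes the problem fully only for an error-free confounder.

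A reader might also infer that the main result is at risk. It is not: the synbiotic-versus-placebo comparison is randomised and is not confounded in this way. This is a worthwhile and cheap improvement to the secondary analyses.

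**What to change.** In Statistical analyses and power:

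1. Report each gut–function and gut–lean-mass association twice: unadjusted, and adjusted for change over the same interval in key dietary intakes (for example energy, protein and fibre) and in PASE, if it is collected at each visit. Use partial correlation, change-on-change regression, or visit-level terms in the mixed models.
2. Include the same variables in the SEM.
3. Delete the statement that the SEM shows relationships not to be coincidental, and say that any causal reading depends on there being no omitted common cause.
4. Treat the adjusted result as a check on confounding, not a pass/fail rule. Greater activity may result from better function, and adjustment could then remove part of a true link.
5. Keep these post-randomisation variables out of the primary comparison between arms.

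The cost is wording and a few degrees of freedom: about 9% more variance at n = 52 and 6% at n = 74 with four uninformative covariates. The diet data are already collected; whether PASE is available at each visit needs confirming. Residual confounding from measurement error will remain and should be acknowledged.

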#### Study duration

Participant involvement will be approximately 22 weeks. This will consist of a screening period of no longer than 2 weeks, a 16-week intervention period, and a 4-week follow-up period. Each participant will attend a screening visit, during which eligibility will be confirmed and informed consent will be obtained. Study investigational product (IP) will be initiated within 2 weeks following successful screening (at baseline visit). Each participant will subsequently attend 3 further visits: mid-intervention at 8 weeks, an end-of-intervention visit at 16 weeks, and a follow-up visit at 20 weeks. Study endpoints will be evaluated at each visit as discussed below. The trial design is outlined in Fig. 2.

**Fig. 2 Fig2:**
[figure not shown]
Study flow chart

#### Study participants

Approximately 74 participants will be enrolled to receive oral synbiotic formulation or placebo (*n* = 37 per group), daily for 16 weeks. Community-dwelling male and female participants between 60 and 85 years of age (inclusive) will be enrolled.

### Eligibility

#### Inclusion criteria

To be eligible for enrolment into the study, participants must meet all of the following:Evidence of a personally signed and dated information consent form (ICF) document indicating that the participant has been informed of all pertinent aspects of the study.Healthy adults* who are determined by medical history and clinical judgment of the investigator to be eligible for inclusion in the study.

*Note: Healthy participants with pre-existing stable disease, defined as disease not requiring significant change in therapy or hospitalization for worsening disease within 6 weeks before enrolment, can be included.(3)Male and nonchildbearing-potential female adults between 60 and 85 years of age (inclusive) at the time of enrolment (signing of the ICF).

Female participants of nonchildbearing potential must meet at least 1 of the following criteria:Postmenopausal status, defined as follows: cessation of regular menses for at least 12 consecutive months with no pathological or physiological cause;Have undergone a documented hysterectomy and/or bilateral oophorectomy;Have medically confirmed ovarian failure.

All other female participants are considered to be of childbearing potential.(4)Willing and able to comply with scheduled visits, laboratory tests, and other study procedures.(5)Willing to refrain from consuming probiotic and/or prebiotic supplements as well as foods that contain naturally occurring probiotics (e.g., fermented foods with live, active cultures such as yogurt, kefir, kombucha, kimchi, curd, buttermilk) from enrolment (Screening) until the end of the study.(6)Able to walk 10 m.(7)Able to get up from a chair.(8)BMI between 18 and 30 (inclusive) and body weight of at least 40 kg.

